## Frequency and duration of follow-up

The primary and secondary outcomes ii, iii, iv, and v will be collected at 3, 6 and 12 months after the end of treatment (and the end of the intervention). Secondary outcome i will be collected at 3 months only.

The follow-up period is for 12 months to determine intervention sustainability. Participants will be contacted by telephone prior to each follow-up assessment to remind them of their participation in the study and to ask their preference for follow-up assessment (postal, email/internet or via clinic attendance).

---

 Incidence data on rectal gonorrhoea will be collected as this is directly related to the risky sexual behaviour that we are assessing in this trial i.e. directly related to condom use.

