### Recruitment procedure

The data collection plan is tailored to the standard patient care protocols stipulated in the BASHH guidelines for PEP, and the clinical processes in use at the recruitment sites. PEP is available from GUM or via Accident & Emergency (A&E). Patients are routinely prescribed a 5-day course of PEP medication at general GUM clinics, or at A&E departments outside of GUM hours. Patient access routes then merge at dedicated PEP clinics at GUM within 5 days of initial prescription. Recruiting at the GUM clinic will ensure all patients who are prescribed the full course of PEP (28 days) are included in the trial from either access route. Eligible participants will be identified by a research nurse/ health advisor at the GUM clinic and given study information and consent forms.

Participants will have a 2-week window in which to consent and return baseline measures. This two week period allows the recruitment of patients at an early stage in their prescription, but at a time when their immediate anxiety should be reduced and they are able to give considered, informed consent.

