### **Trial treatment arms**

#### **Control group: Treatment/management as usual**

Both of the groups will receive 'treatment/management as usual': Patients are initially seen by a HA/SpN for an initial consultation, 5 day prescription of PEP and blood tests (for HIV, Hepatitis B and liver function). Patients receive their first follow-up appointment 5 days later to receive further PEP (if HIV-ve). After the 28 day treatment regimen patients receive either a face-to-face or telephone appointment with the HA/SpN to discuss their sexual health, adherence to PEP and the blood test results. At 4 months after exposure (3 months after the end of PEP) patients are recalled by the HA for HIV testing. In order to assess the impact of the intervention on outcome measures and IMB constructs, those allocated to control group 1 will be asked to complete all measures at 0,3,6, and 12 months.

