### **Intervention group**

#### **Procedure**

The intervention group will receive 'treatment and management as usual' plus the addition of an intervention which will be delivered as two telephone sessions employing motivational interviewing (MI) augmented with information and skills building based on the IMB model of behaviour change. The first call will be made within one week of the participant being consented into the trial and after baseline assessments are received. The second call will occur 7 days (+/-2 days) later. The intervention will be completed by the end of the 28 day course of PEP. A telephone format is proposed to allow the same person to conduct all interventional sessions to control for provider differences and to facilitate recruitment from a wide geographical area in an economical manner. If shown to be effective, this intervention would be sustainable within an improved routine care model.

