## Measures

**Primary outcome:** The proportion of risky sexual practices.

Risk Behaviour outcome measure

A Risk Behaviour outcome measure has been developed to include items of potential HIV transmission-risk sexual behaviour: number of episodes of unprotected anal intercourse (UAI) (receptive and insertive) over a three month time period with individuals of unknown or HIV positive status, consistency of condom use, number of partners using no protection.

(Unprotected receptive oral sex with an HIV+ve person is associated with minimal HIV transmission risk and thus is not included).

**Secondary outcomes** (and method of assessment):

- i) Levels of adherence to PEP treatment (Morisky Medication Adherence Scale (MMAS) [32] adapted for use in PEP)
- ii) Number of subsequent courses of PEP (self-report and medical record review).
- iii) Levels of motivation to avoid risky sexual behaviours ('Measures of Motivation to Perform AIDS Preventive Behavior' questionnaire [33] adapted for use with MSM. This questionnaire provides assessment of attitudes, subjective norms and behavioural intentions in relation to HIV risk-reduction).
- iv) Levels of HIV risk-reduction information/ knowledge ('Health and Relationships Survey' [33] adapted for use with MSM. Items are summed to form an HIV prevention information scale score).
- v) Levels of risk reduction behavioural skills ('Behavioral Skills Measure' [33]. This consists of two subscales which assess the perceived difficulty of reducing HIV risk behaviour and the perceived effectiveness of methods to reduce risk).
- vi) Diagnosis of anal gonorrhoea
- vii) Diagnosis of HIV.

With the exception of adherence, all outcome measures will use a retrospective recall period of 'the past 3 months'.

Other factors assessed by self-report questionnaire at each time point will be alcohol and substance use. Socio-demographic (age, ethnicity, education, employment, relationship status) will be assessed at baseline. Experience of treatment side-effects will be assessed using a previously used measure at 3 month together with the measure of adherence.

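### PEP adherence rests on one questionnaire about 3 months after the course ends, and the stated windows let the calls fall late in, or after, the 28 days

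*Protocol*

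**What the plan says.** All places are in the Protocol.

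- **Instrument** (Measures): "Levels of adherence to PEP treatment (Morisky Medication Adherence Scale (MMAS) [32] adapted for use in PEP". The same section states: "With the exception of adherence, all outcome measures will use a retrospective recall period of 'the past 3 months". No other recall period is given for adherence.
- **Timing** (Frequency and duration of follow-up): "Secondary outcome i will be collected at 3 months only". The other questionnaire outcomes "will be collected at 3, 6 and 12 months after the end of treatment (and the end of the intervention", so the clock starts at the end of PEP and the two end dates are treated as one. The usual-care description agrees on the calendar: "At 4 months after exposure (3 months after the end of PEP) patients are recalled by the HA for HIV testing".
- **Enrolment** (Recruitment procedure): men reach the dedicated PEP clinic no later than 5 days after first prescription. "Participants will have a 2-week window in which to consent and return baseline measures". The start of that window is not stated.
- **Calls** (Intervention group, Procedure): the first call comes no more than a week after consent and once baseline forms are in. The second follows 7 days later, give or take 2. Then: "The intervention will be completed by the end of the 28 day course of PEP".
- **Other adherence data**: after the 28 days, in both arms, "patients receive either a face-to-face or telephone appointment with the HA/SpN to discuss their sexual health, adherence to PEP". Duration and content of intervention also names a medical notes review as a source of adherence data, but Measures does not list it as the method for this outcome.

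**The concern.** There are two linked problems.

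First, a 28-day behaviour is asked about long after it ended, although both arms already have a contact after the course at which adherence is discussed. Long recall adds measurement error, and the men reporting know their allocation.

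Second, a randomised comparison can only detect an effect on doses that come after the intervention starts. If a large part of the course has passed before the first call, a score for the whole course mixes doses that could respond with doses that could not, and the difference between arms shrinks toward zero. A null result on the secondary aim would then be hard to interpret: the intervention may not work, or it may have come too late to show.

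The same windows also conflict with the statement that the intervention ends within the course. That statement matters elsewhere, because follow-up is timed from a date treated as the end of both treatment and intervention, and Treatment fidelity relies on delivery within the intervention period to keep the dose equal.

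**Working it through.** **Inputs** (day 0 = first PEP dose): clinic visit by day 5; 2-week (14-day) window; first call up to 7 days after consent; second call 5, 7 or 9 days after the first; course of 28 days.

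**The plan's own figure**: both calls done by day 28. Latest dates under each reading of the 2-week window:

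| Window counted from | Latest entry | Latest first call | Second call (gap 5 / 7 / 9) |
|---|---|---|---|
| First prescription | 0 + 14 = day 14 | 14 + 7 = day 21 | day 26 / 28 / 30 |
| Clinic visit on day 5 | 5 + 14 = day 19 | 19 + 7 = day 26 | day 31 / 33 / 35 |

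Day 28 is met exactly on the first reading with the nominal gap, and is exceeded by up to 2 days with the longer gap. On the second reading, even the shortest gap overruns at the outer limit.

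**Latest entry compatible with day 28** when the first call uses its full week: 28 − 7 − gap = day 16, 14 or 12 for gaps of 5, 7 or 9 days. The windows allow entry on day 14 or day 19.

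**How much of the permitted range overruns.** Take whole days: 15 entry lags × 8 first-call lags × 5 gaps = 600 combinations. Those ending after day 28 number 4 of 600 (0.7%) on the first reading and 80 of 600 (13.3%) on the second, with the clinic visit fixed at day 5. This counts what is permitted. It is not a forecast, because the protocol gives no distribution of enrolment times.

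**Recall interval.** Three months is about 91 days, so the questionnaire falls near day 28 + 91 = 119. The last dose is recalled after about 91 days and the first after about 119. The figure is approximate, because the form is sent ahead of the 3-month appointment, and the gap is longer for men who stop PEP early.

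**Share of the course still open at the first call**: (28 − day of call) / 28.

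- Day 5: 23/28 = 82%
- Day 14: 14/28 = 50%
- Day 21: 7/28 = 25%
- Day 26: 2/28 = 7%

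If the score weights all 28 days equally and the effect on later doses is uniform, the visible effect is that fraction of the true effect on later doses.

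**The case against.** The strongest reply is that the window conflict is an edge case. Recruitment procedure says the window is meant to catch men early in their prescription, which fits counting from prescription. On that reading the nominal schedule is 14 + 7 + 7 = day 28, just as stated, and only the 2-day tolerance overruns. The day-28 sentence could also be read as a cap on the windows, and since the call clock runs from consent, prompt consent brings the calls forward. This stands as a limit on size. It does not remove the conflict: no start is given for the window, and nothing says which rule prevails.

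The notes review is a second fair point. A reader might infer that the trial has no other adherence data; the protocol does not support that. But the review is not named as the method for this outcome, whereas record review is named for repeat PEP courses.

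A reader might also infer that half the men will be missing at 3 months, because the sample-size text allows for 50% retention. That figure has no time point, in a study followed to 12 months, and the fullest chasing is planned at 3 months. Loss specific to this outcome cannot be read from it.

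Whole-course scoring is likewise an inference. The scale is adapted, its wording is not shown, and an adapted Morisky scale is not a dose count, so the percentages above illustrate the mechanism and are not estimates.

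Finally, earlier collection does not cure unblinding, and the post-course appointment has no fixed date, so a form completed there could precede a late second call.

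**Conclusion.** The point holds for a secondary outcome and leaves the primary outcome untouched. As written, the secondary aim rests on one self-report questionnaire recalled over about 91 to 119 days, about a course that may be partly or largely over before the first call. The windows permit completion up to day 30 or day 35, against a stated limit of day 28.

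The dilution figures, from 82% visible for a day-5 call to 7% for a day-26 call, depend on whole-course scoring and a uniform effect, neither of which the protocol states. Day 26 also needs every delay at its maximum and the later start of the window. A reader might infer that most men would be called that late; the protocol gives no enrolment timing to support it. The recall interval and the timing conflict depend on none of these assumptions.

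**What to change.** 1. Have both arms self-complete the adapted adherence scale at the existing post-course appointment, or by post or online at that time if the contact is by telephone. Use identical wording in both arms, state the period the items cover, and date each form. Keep the 3-month item as a check. A stem restricted to doses after randomisation is not advised: controls may not know that date, and it departs further from the scale.
2. Record the dates of PEP start, randomisation and each call. The share of the course left at randomisation is defined in both arms, so adherence can be interpreted against it. Call dates exist in the intervention arm only and are descriptive. This makes dilution visible; it does not remove it.
3. Reconcile Recruitment procedure, the intervention Procedure section, and Frequency and duration of follow-up: where the 2-week window starts, how the call windows relate to the 28-day statement, and which end date starts the follow-up clock. How this is settled is for the trial team.
4. Reconcile Duration and content of intervention with Measures on whether the notes review forms part of the adherence outcome.

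The cost is one short extra form, with some non-response of its own, a few recorded dates, and clarified text.

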## **Barriers to implementation**

A recent review [20] highlighted that the recruitment of MSM participants was the most challenging aspect of similar behavioural intervention studies. To overcome these barriers we are employing strategies to ensure that recruitment and retention are maximised, including: the refinement of assessment materials with the MSM community; the use of a telephone-based intervention to overcome geographic boundaries, time constraints and fear of public exposure as an MSM; the recruitment of individuals seeking PEP by the HIV nurse specialist rather than the recruitment of high risk individuals from the community.

## **Analyses plan and power calculation**

For the analysis of main effects for the primary outcome a mixed-design ANCOVA will be used with one between-groups factor (treatment vs. control) and one within-groups factor (baseline, 3-, 6- and 12-month measures). For this analysis the estimated effect size is  $f=0.2$  (based on a moderate estimate of effect size from a meta-analysis [24] of one to one interventions to reduce UAI in MSM). 90% power at 0.05 level of significance requires a sample of 250 (125 in each arm). Secondary outcomes will be analysed for the same effect size but with significance adjusted to 0.01 and power to 80%.

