### Baseline and follow-up assessments

Participants enrolled into the study will be asked to self-complete a questionnaire at four time points during the study (at 0,3,6,12 months). The baseline questionnaire will be administered at the recruitment stage, and upon receiving the consent forms and baseline assessments, participants will be randomly allocated to either intervention or control conditions (see randomisation section).

The second questionnaire will be posted to patients or accessed via email/the internet (as per consent) prior to their 3-month follow-up appointment with the clinic. Any patients who have not returned completed questionnaires before their '3-month' follow-up will be sent repeat copies (as per consent), and subsequently called on the telephone (if consented), and finally, may be approached by study staff at their clinic appointment.

The third questionnaire will be posted to patients or accessed via email/the internet (as per consent) 6 months after the end of PEP. Patients not returning their questionnaires will be sent repeat copies, and subsequently called on the telephone (as per consent). Those with a '6-month' follow-up appointment (depending on the recruitment site) and who have failed to return their questionnaire will be approached by study staff at their clinic appointment.

---

 Maximum of 2 repeat copies and 1 text/call/email if consented by patient.

The fourth questionnaire will be posted to patients or accessed via email/the internet (as per consent) 12 months after the end of PEP. Repeat copies, and subsequent telephone calls, will be used as reminders.

The recruitment period is for 12 months to allow sufficient numbers of participants to be recruited. A sample size of 250 (allowing for a 75% recruitment rate and 50% retention rate) is achievable within the time-frame and we anticipate that numbers will be higher given the increasing trends for PEP requests.

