### **Randomization and blinding**

The random allocation sequence will be computer generated in advance of the trial. Participants will be randomised after consent and collection of baseline measures. The recruiting staff will not have access to the results of randomisation prior to recruiting the participant. AP will be given the results of the randomisation on a case by case basis by a custodian who is unconnected to the project. Randomisation will occur within each clinic. A statistician (MH) will generate the allocation sequence (who will be blind to the identity of the individuals involved). This is a single-blind trial, given the nature of the behavioural intervention, blinding of participants is not feasible and the interventionist (AP) will know that all those he contacts are in the intervention arm. The PI and statistician will be blind to individual results during the trial and the allocation-to-trial-arm coding will be revealed when the dataset is sealed.

The interventionist (AP) and AP's supervisors will be blind to the baseline and follow-up measures which will not inform the delivery of the intervention. Anonymised measures will be entered onto the database by a person unconnected to the project.

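### The protocol makes the pre-randomisation baseline one of four outcome occasions and does not name the treatment contrast; read literally, the group main effect estimates three quarters of the follow-up effect

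*Protocol*

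**What the plan says.** The protocol's section on the analysis plan and power calculation gives the primary analysis in one sentence. It opens: "For the analysis of main effects for the primary outcome a mixed-design ANCOVA will be used". The rest of that sentence lists the design factors, namely "one between-groups factor (treatment vs. control) and one within-groups factor (baseline, 3-, 6- and 12-month measures"). It names no group-by-time interaction, follow-up contrast, primary time point or covariate.

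The same section takes an effect size of f = 0.2, "based on a moderate estimate of effect size from a meta-analysis [24] of one to one interventions to reduce UAI in MSM", and states that "90% power at 0.05 level of significance requires a sample of 250 (125 in each arm").

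The section on randomisation and blinding says: "Participants will be randomised after consent and collection of baseline measures". The section on frequency and duration of follow-up says: "The primary and secondary outcomes ii, iii, iv, and v will be collected at 3, 6 and 12 months after the end of treatment". There are therefore three post-randomisation occasions and one pre-randomisation occasion.

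Only the protocol was available. A separate analysis plan may exist.

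**The concern.** A measurement taken before randomisation cannot carry a treatment effect. In expectation the arms are equal at baseline. If baseline is one of four equally weighted outcome levels and the group main effect is the test, one zero is averaged with three real differences. The result understates what happened after the intervention by a quarter, whatever the correlation between occasions and whatever the pattern over follow-up.

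Baseline is also most useful on the other side of the model. As a covariate it removes between-person variation; as an outcome level it only adds to what is averaged.

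What is at stake is the size of the reported primary effect and, on one reading, whether the trial has the power it states. If the primary estimate feeds the economic model, which converts behaviour change in the trial into averted transmissions, the understatement would carry over.

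**Working it through.** **Inputs from the protocol.** f = 0.2, which for two equal groups is d = 2f = 0.40 SD; N = 250, 125 per arm; significance level 0.05; power 90%; four occasions, the first before randomisation.

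**Assumptions.** Two-sided test (sidedness is not given). Equal variances and equal correlation ρ between all occasions (ρ is not given, so 0.3, 0.5 and 0.7 are shown). A difference of 0.40 SD at each follow-up. Complete data. Variances are in SD² units per person, and z = effect / √(4 × variance / 250).

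**1. The protocol's own figure.** For a single two-group comparison, z = 0.40/√(4/250) = 3.16, giving 88.5% power. This is close to the stated 90%. Solving for N gives 264 rather than 250.

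**2. Dilution.** The expected four-occasion difference is (0 + 0.40 + 0.40 + 0.40)/4 = 0.30 SD, which is 3/4 of 0.40. A simulation at ρ = 0.5 gave mean estimates of 0.304 (four occasions) and 0.404 (three follow-ups).

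**3. Power under each reading, N = 250.**

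- A: group main effect over four occasions, baseline not a covariate. Effect 0.30; variance (1 + 3ρ)/4.
- B: three follow-ups, baseline unused. Effect 0.40; variance (1 + 2ρ)/3.
- C: three follow-ups, baseline as covariate. Effect 0.40; variance (1 + 2ρ)/3 − ρ².
- D: four occasions with baseline also as covariate. Effect 0.30; variance v − v², where v = (1 + 3ρ)/4.
- E: group-by-time test on 3 df. The differences centred on their mean are −0.30, 0.10, 0.10, 0.10, with sum of squares 0.12. Noncentrality is 62.5 × 0.12/(1 − ρ) = 7.5/(1 − ρ), with 3 and 744 df.

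| Reading | ρ = 0.3 | ρ = 0.5 | ρ = 0.7 |
|---|---|---|---|
| A | z 3.44, 93% | z 3.00, 85% | z 2.69, 77% |
| B | z 4.33, 99% | z 3.87, 97% | z 3.54, 94% |
| C | z 4.75, >99% | z 4.90, >99% | z 5.68, >99% |
| D | z 4.75, >99% | z 4.90, >99% | z 5.68, >99% |
| E | noncentrality 10.7, 79% | 15.0, 92% | 25.0, 99% |

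Example at ρ = 0.5:
- A: 0.30/√(4 × 0.625/250) = 3.00
- C: 0.40/√(4 × 0.4167/250) = 4.90
- D: 0.30/√(4 × 0.2344/250) = 4.90

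C and D give the same z because the covariate absorbs the baseline part of the four-occasion mean. The estimate under D is still 0.30, not 0.40.

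**4. Reading across.** A has less power than B at each ρ shown, so baseline as an outcome level does harm by itself when it is not adjusted for. A exceeds 90% at ρ = 0.3 and misses it at 0.5 and above.

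**The case against.** The strongest objection is that the protocol does not clearly say that the group main effect is the test. The phrase about main effects may mean the main treatment comparison, as distinct from the secondary outcomes. Listing baseline as a level fits a group-by-time test, and the first hypothesis speaks of a reduction relative to usual care, which is the language of change. This stands: reading E is open, it has no dilution, and its power rises with ρ. The sample size does not settle the matter. A plain two-group comparison gives 264, not 250, and E comes near the stated power at ρ = 0.5.

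A second objection is that ANCOVA implies a covariate, that baseline is the obvious one, and that naming covariates is commonly left to the analysis plan. This also stands. The missing covariate name is not a fault in itself, and under reading D no power is lost. The shrunken estimate remains, with baseline serving as both outcome and predictor.

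A third is that f = 0.2 is stated for this analysis, so it might already describe the four-occasion average. That cannot be excluded. However, the protocol draws it from a meta-analysis of interventions to reduce the behaviour, and nothing suggests that a pre-treatment value was averaged in.

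A reader might infer that the plan certainly discards most of its power, needing 1.9 to 4.4 times as many men as the adjusted analysis (the squared ratio of z in C to z in A). The documents do not support that as fact, since it holds only under reading A.

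**Conclusion.** The point holds as a defect of specification. Read literally, the group main effect estimates 3/4 of the mean follow-up effect, with or without baseline adjustment. The amount follows from pre-randomisation measurement and equal weighting of the four occasions alone.

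The loss of power is conditional. It applies if the main effect is tested without baseline as covariate, and its size depends on an unstated correlation: about 93%, 85% and 77% at ρ = 0.3, 0.5 and 0.7, under compound symmetry, complete data and 0.40 SD at each follow-up. Under the group-by-time reading there is no dilution, and the corresponding figures are 79%, 92% and 99%.

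Two stronger inferences are not supported. The first is that the test is invalid: with no treatment effect the expected contrast is zero, so dilution does not produce false positives. The second is that power should be recomputed at half the sample because of dropout. The protocol says of its target: "A sample size of 250 (allowing for a 75% recruitment rate and 50% retention rate) is achievable". Whether that allowance is sound is a separate question.

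Because the sentence defines the primary analysis and admits readings with different estimates and different power, it should be settled before the allocation is revealed.

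**What to change.** Remove baseline from the within-groups factor. Model the 3-, 6- and 12-month outcomes with the baseline value of the outcome as covariate and with terms for arm, time and arm-by-time. Name the treatment contrast in advance, for example the arm difference averaged over the three follow-ups, and report the time-specific differences to address sustainability. The choice of contrast belongs to the sponsor; what matters is that one is fixed.

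On the assumptions above, the averaged contrast has more than 99% power at each correlation shown and estimates the full 0.40 SD. The comparison with a group-by-time test assumes a constant effect over follow-up.

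The cost is wording only. Baseline and all three follow-ups are already collected, and the sample size need not change on this account.

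### The same 250 serves as the number needed for 90% power and as the figure tied to 50% retention, and the readable protocol does not say how many men are to be randomised

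*Protocol*

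**What the plan says.** Protocol, Analyses plan and power calculation: the primary outcome is analysed by a mixed-design ANCOVA with one between-groups factor (the two arms) and "one within-groups factor (baseline, 3-, 6- and 12-month measures"). The effect size is f = 0.2, "based on a moderate estimate of effect size from a meta-analysis". The conclusion is that "90% power at 0.05 level of significance requires a sample of 250 (125 in each arm"). The section does not mention attrition.

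Protocol, Baseline and follow-up assessments, in the paragraph on the 12-month recruitment period: "A sample size of 250 (allowing for a 75% recruitment rate and 50% retention rate) is achievable within the time-frame".

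Protocol, Frequency and duration of follow-up: "The follow-up period is for 12 months to determine intervention sustainability". Outcomes are collected at 3, 6 and 12 months. The time point to which the 50% retention refers is not given.

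The readable text gives no number to be randomised other than the 125 per arm in the power section. The participant flowchart (Figure 2) could not be read for this review.

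**The concern.** The power section presents 250 as what the test needs. The assessments section mentions the same 250 when describing what a year of recruitment can deliver, and links it to losing half the men. With 50% retention, the number randomised and the number analysed differ by a factor of two, so 250 can be only one of them.

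A team that follows the only per-arm figure in print would randomise 125 per arm. If half are then lost, about 62 or 63 per arm remain. A null primary result could be reported as coming from a trial with 90% power when the protocol's own retention figure does not support that claim.

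**Working it through.** **Inputs.** From the power section: f = 0.2, significance level 0.05, power 90%, two equal arms, 250 in total, four measures. From the assessments section: 75% recruitment and 50% retention. Assumptions: two-sided test; standardised difference d = 2f = 0.4; equal correlation ρ between any two measures on the same man, which the protocol does not state, so a range is shown; men who are lost contribute no data.

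**1. The protocol's own figure.** Noncentral F test, two groups, 1 and N − 2 degrees of freedom, λ = N·f².
- N = 250: λ = 250 × 0.04 = 10, power 88.3%.

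This is close to the stated 90%. On this formula 250 is an uninflated, analysable number and contains no allowance for loss.

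**2. Applying the protocol's 50% retention.**
- 250 randomised: 250 × 0.5 = 125 analysed.
- 250 retained: 250 / 0.5 = 500 randomised (250 per arm), and 500 / 0.75 ≈ 667 approached.
- If 250 is the number enrolled, 250 / 0.75 ≈ 333 are approached.

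**3. Power with 125 analysed, by form of analysis.**

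(a) Single two-group comparison: λ = 125 × 0.04 = 5, power 60.2%.

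(b) Group main effect over the four levels named in the power section. Randomisation follows the baseline measures (Randomization and blinding), so the expected baseline difference is zero. With 0.4 SD at each follow-up, the difference in four-measure means is (0 + 3 × 0.4)/4 = 0.3. The variance of a man's mean is (1 + 3ρ)/4, and λ = 125 × 0.3² / [4 × (1 + 3ρ)/4] = 11.25/(1 + 3ρ).

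(c) Group main effect if the full f = 0.2 held at all four measures, baseline included: λ = 5 × 4/(1 + 3ρ).

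(d) Baseline as covariate, with the three follow-ups averaged and 0.4 SD at each. The residual variance is (1 + 2ρ)/3 − ρ², and λ = 125 × 0.4² / (4 × residual variance) = 5/residual variance.

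| ρ | (b) λ | (b) power | (c) λ | (c) power | (d) λ | (d) power |
|---|---|---|---|---|---|---|
| 0.3 | 5.92 | 68% | 10.53 | 90% | 11.28 | 91% |
| 0.5 | 4.50 | 56% | 8.00 | 80% | 12.00 | 93% |
| 0.7 | 3.63 | 47% | 6.45 | 71% | 16.13 | 98% |

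Across these forms, power at 125 analysed runs from about 47% to 98%. Form (b) is closest to the wording of the power section, which speaks of main effects and lists baseline as a level of the within-groups factor.

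**The case against.** The strongest reply is that the assessments section already deals with retention. Its wording, "allowing for a 75% recruitment rate and 50% retention rate", can be read to mean that 250 men remain after both losses. That agrees with the power section, where 250 is what the test needs. The protocol never calls 250 a recruitment target or says that 250 will be randomised. This stands: the documents do not establish a shortfall. But it does not supply the missing number. On this reading about 500 men must be randomised, and the only per-arm figure printed is 125.

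A second reply is that the planned analysis uses repeated measures and is called an ANCOVA, so the single-comparison 60% may be pessimistic. This also stands in part. If baseline is a covariate and the follow-ups are averaged, 125 men could give more than 90%. Men lost late may also contribute earlier measures. However, the power section puts baseline among the within-groups levels and states no correlation, so the gain cannot be assumed.

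Two stronger readings are therefore tempting but not supported:
- A reader might infer that 90% power cannot be reached unless 500 men are randomised. That depends on the unstated correlation and the form of the model, and form (d) is a counterexample.
- A reader might infer that 250 is itself too small, because the simple test gives 88.3%. The gap is under two points, and a baseline correlation of about 0.22 in the ANCOVA would close it. No correction is needed on that account.

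**Conclusion.** The point holds as an unresolved double use of one number, with a possible loss of power on one of its two readings. If 250 is the retained number, the stated power is about right and the protocol omits the roughly 500 to be randomised. If 250 is the number randomised, about 125 are analysed and the stated 90% is not supported: about 60% for a single comparison, and about 47% to 68% for the four-level main effect with no baseline difference, although a baseline-adjusted analysis of the averaged follow-ups could exceed 90%.

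These figures rest on a two-sided test, d = 0.4 at each follow-up, equal correlations of 0.3 to 0.7, and no data from men who are lost. Figure 2 may give a number randomised; if it does, the text should agree with it. Severity: should-fix.

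**What to change.** In both the power section and the assessments section, state two separate numbers: men to be randomised and men expected to be analysed. Give the time point to which the 50% retention applies and the within-person correlation assumed. Then:
- If 250 is the number randomised, restate the power for about 125 analysed under the stated model, and make explicit whether baseline is a covariate or a level of the within-groups factor.
- If 250 is the number analysed, state 500 randomised (250 per arm) and about 667 approached, and check that the claim of feasibility within 12 months refers to those numbers.

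The cost is the rewording of two sentences and one power calculation. If 500 was always intended, the design does not change. If 250 was intended, the stated power may become less favourable, and the sponsor would then decide whether to accept it or recruit more men.
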